#### Standardized training cases

Following the workshop, each TMCU interventionist will complete training cases involving SP portrayal of a marijuana-using teen. Each case will be structured as a 30–45 min interaction, to occur at arranged times in interventionists’ regular workspace. The workshop trainers (BH, DW) will score corresponding audio-recordings with an MI fidelity instrument [73], providing written feedback on performances relative to these conceptually derived behavioral fidelity benchmarks (1) reflection-to-question ratio (R:Q), (2) percent open questions (%OQ), and (3) percent complex reflections (%CR).

#### Post-training assessment

Upon training conclusion, interventionists complete a web-based survey assessment of MI knowledge and attitudes, adoption readiness, and training satisfaction. Additionally, interventionists will repeat the audio-recorded SP encounter to assess the impact of training on TMCU fidelity.

#### Staff randomization

At training conclusion, the trial coordinator (LM) will allocate via urn randomization TMCU interventionists to receive technical assistance via (1) a ‘gold-standard’ weekly group session, or (2) ‘as-needed’ individual sessions triggered by fidelity drift alarm. A shared feature of both methods is the direct oversight of the TMCU purveyor (DW), who will monitor fidelity in review of session audio-recordings and provide numeric feedback to interventionists regarding behavioral fidelity indices (i.e., R:Q, %OQ, %CR). Notably, the technical assistance methods differ in format and anticipated frequency of occurrence, with differential cost expected.

The third EPIS phase focuses on TMCU implementation at participating schools over a 24-month period. This includes recruitment and randomization of self-referring students, baseline student assessment, TMCU delivery, fidelity-monitoring and technical assistance, and student outcome assessments (3-, 6-month follow-ups). To inform cost-benefit and cost-effectiveness analyses, both purveyor and interventionists complete weekly continual time-logs documenting effort in select activities. Figure 3 offers a CONSORT flow diagram depicting trial procedures for self-referring students.

**Fig. 3 Fig3:**
[figure not shown]
CONSORT flow diagram for students

#### Student recruitment

At each school, TMCU interventionists will contribute to on-site promotion via classroom presentations and cafeteria exhibits. Self-referring students will have a TMCU interventionist read a brief explanation of the trial, and if interested will be directed to a web-based assent/consent form with contact information for university-based research staff. Students will provide informed assent/consent prior to interventionist conduct of a brief, confidential screening interview to determine eligibility. Inclusion criteria are that students be (1) 14–19 years old, (2) enrolled in 9th–12th grade, and (3) active marijuana users (9+ days in prior month). Students will be excluded if they are not fluent in English, have a thought disorder, or refuse to be randomized to condition. Ineligible students will receive standard marijuana resources/referrals.

#### Student randomization

Upon determination of eligibility, students will be randomized in a 2:1 ratio to TMCU or waitlist/control. This will occur after blocking by student gender and grade-level, independently at each school. The trial seeks 250 student participants during its 24-month period of TMCU implementation.

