### Trial procedures

A procedural chronology begins with initial exploration of participating school contexts. This involves recruitment of schools, assessment of their setting attributes, and identification of staff candidates to serve as TMCU interventionists.

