#### Baseline student assessment

All student assessments occur over encrypted web servers. Baseline assessment will gather demography, contact information, and TMCU personal feedback report data on marijuana use, problems, motives, perceptions, and self-efficacy to abstain.

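### Student randomization is placed before the web baseline, and nothing withholds the allocation until the baseline is complete, so in the TMCU-versus-waitlist comparison baseline self-report and retention could be affected by it

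*Protocol article*

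**What the plan says.** The Protocol article introduces its procedures as a time sequence: "A procedural chronology begins with initial exploration of participating school contexts". For students the steps run as follows.

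- Student recruitment: "Students will provide informed assent/consent prior to interventionist conduct of a brief, confidential screening interview to determine eligibility". The use criterion at this step is a threshold, "active marijuana users (9+ days in prior month".
- Student randomization: "Upon determination of eligibility, students will be randomized in a 2:1 ratio to TMCU or waitlist/control". This is done within each school, after blocking on gender and grade.
- Baseline student assessment, the next section: "Baseline assessment will gather demography, contact information, and TMCU personal feedback report data on marijuana use, problems, motives, perceptions, and self-efficacy to abstain".

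The overview of the implementation phase, at the end of the Staff randomization section, gives the same order in a list: "This includes recruitment and randomization of self-referring students, baseline student assessment, TMCU delivery, fidelity-monitoring and technical assistance, and student outcome assessments".

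Table 2 and the Students section make baseline the first of three time points (baseline, 3 and 6 months) for the outcome instruments, including the one that yields recent marijuana use. Hypothesis testing and analytic approach expects a larger reduction in use frequency with TMCU than with waitlist. The Limitations section acknowledges that use is student-reported, without biological testing.

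**The concern.** Baseline use is the starting point from which the reduction is measured. If it is collected after allocation from students who know their arm, it is no longer protected by randomization. A student told to wait 6 months and a student about to start may describe the same past month differently. Any such difference feeds into the time-by-arm contrast.

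The second risk is loss between allocation and baseline. Locator data are collected at baseline (Table 2; Baseline student assessment), and Student outcome assessments relies on those data to limit attrition. A student who stops after allocation but before the web survey is therefore randomized with neither a baseline outcome nor the details needed for tracing. The incentive is not symmetric. For a TMCU student the baseline supplies the personal feedback report reviewed in the second session, while a waitlisted student has no such immediate use for it.

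At stake is the estimate of TMCU effectiveness against waitlist, which has its own hypothesis and power target and feeds the cost-effectiveness ratio in Cost analyses.

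**Working it through.** **Order of steps.** There is no stated figure to reproduce, so the first check is textual.

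1. The trigger for randomization is eligibility. Eligibility is settled by a brief interview held by the interventionist, not by the web baseline.
2. The implementation-phase list puts recruitment and randomization first, then baseline assessment, then TMCU delivery. This agrees with the order of the sections and does not depend on it.
3. No sentence puts the baseline before randomization or holds the allocation back until it is complete.
4. The only masking described is that of the fidelity raters, with respect to technical assistance method (Interventionists section). Waitlisted students receive TMCU only after 6 months (TMCU delivery), so once told their arm they cannot be unaware of it.
5. Screening asks about prior-month use only against the 9-day threshold. It is not described as the outcome baseline and so does not stand in for it.

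**Illustration of size.** From the article: N = 250, 2:1 allocation, d = .35. Assumed, because the article gives neither: a between-arm shift b in baseline reporting (in SD units) and a baseline/follow-up correlation rho. The true effect is set to zero.

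- Bias of the unadjusted change contrast: b. Bias of a baseline-adjusted contrast: rho × b.
- Control group size n = 250/3 = 83.3, so f = √(1/n + 1/(2n)) = √0.018 = 0.134.
- SE of the change contrast: √(2(1 − rho)) × f, which is 0.134 at rho = 0.5. SE of the adjusted contrast: √(1 − rho²) × f, which is 0.116.
- Two-sided type I error: Φ(bias/SE − 1.96) + Φ(−bias/SE − 1.96).

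Results at rho = 0.5:

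| b (SD) | Change: bias as share of .35 | Change: type I error | Adjusted: bias as share of .35 | Adjusted: type I error |
|---|---|---|---|---|
| 0.05 | 0.05/0.35 = 14% | 0.07 | 0.025/0.35 = 7% | 0.06 |
| 0.10 | 0.10/0.35 = 29% | 0.12 | 0.05/0.35 = 14% | 0.07 |
| 0.20 | 0.20/0.35 = 57% | 0.32 | 0.10/0.35 = 29% | 0.14 |

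Varying rho from 0.3 to 0.7 at b = 0.10 moves the type I error from 0.10 to 0.16 for change and from 0.06 to 0.11 for the adjusted contrast. Adjustment reduces the bias but does not remove it.

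**The case against.** **Disclosure.** The article does not say when students learn their allocation. A reader might infer that they know it when they fill in the baseline; the text does not establish that. Disclosure timing is also a detail that an article may leave to the full protocol. This stands, and it limits the point to what could happen. The stated order, however, is not an omission: the article makes eligibility the trigger and lists randomization ahead of baseline.

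**Firmness of the order.** The procedures are not strictly chronological. Time-logs, for example, are described after the 6-month assessments although they run weekly throughout. Randomization is blocked on gender, which is not an eligibility criterion, and student demography is said to be collected only at baseline, so some information must be available earlier than described. Figure 3, the student flow diagram, is not in the text available here. These points leave some doubt, but none establishes a different order. If Figure 3 shows one, the prose still needs correcting.

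**Reach.** A reader might infer that the trial's main comparison is compromised. It is not. The co-primary aims compare technical assistance methods, for which interventionists are randomized, and the named primary student test parameter is time by technical assistance method. The problem is confined to TMCU versus waitlist.

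**Attrition.** A reader might infer that post-allocation loss breaks the randomized comparison. The article shows no such loss. It excludes students who refuse randomization, pays for assessments, offers TMCU to the waitlist after 6 months and cites follow-up retention of 90% or more in prior TMCU trials. Multilevel models also do not inherently require a complete baseline. The loss is a risk that the order permits, not one that is demonstrated.

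**Conclusion.** The point holds in limited form. As written, an allocation that cannot be masked precedes the self-reported baseline of marijuana use and the collection of locator data, with no stated safeguard. For TMCU versus waitlist, this opens an avoidable route to bias in baseline reporting and to loss after randomization.

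Neither the size nor the direction can be determined from the article. The range of 14% to 57% of d = .35 rests wholly on an assumed reporting shift of 0.05 to 0.20 SD and on an unadjusted change contrast, which the article does not specify; it describes multilevel growth models. With baseline adjustment and an assumed correlation of 0.5 the range is 7% to 29%. No single figure in these ranges should be read as an estimate of the bias. The case for changing the text is that the safeguard is simple and removes this source of bias whatever its size.

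**What to change.** In the Protocol article, make the same statement in the implementation-phase overview (end of Staff randomization), in Student randomization and in Baseline student assessment: eligible, assented students complete the web baseline, including locator data, and only then is the allocation generated. If operations require allocation to be generated earlier, state at minimum that it is disclosed to neither student nor interventionist until the baseline is complete. If allocation is already withheld in practice, one clarifying sentence suffices. Figure 3 should agree with the text.

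The change reorders two existing steps and leaves the sample size of 250 as it is. The cost is a short delay between screening and allocation. Students who do not complete the baseline would then drop out before randomization rather than after it. Trial regulation and current status reports that school recruitment had only begun, so at the time of writing the change could still be made before students enrolled.

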#### Baseline student assessment

All student assessments occur over encrypted web servers. Baseline assessment will gather demography, contact information, and TMCU personal feedback report data on marijuana use, problems, motives, perceptions, and self-efficacy to abstain.

#### TMCU delivery

Trained interventionists will deliver the TMCU to eligible, self-referring students over a 24-month period. This consists of two sessions, each 45 min in duration occurring a week apart. The initial session develops rapport, explores aspects of the student’s marijuana use, and identifies sources of motivation to change. The latter session includes conjoint review of the personal feedback report, with the interventionist eliciting self-motivational statements about reduction or discontinuance of marijuana use and offering advice for such changes. Notably, interventionists deliver TMCU to waitlist-assigned students only after a requisite 6-month intervening period.

#### Purveyor fidelity-monitoring

All TMCU sessions will be subject to fidelity-monitoring by the purveyor (DW). Fidelity will be evaluated via a behavioral coding system with demonstrated validity for evaluating adherence of MI-based interventions [73]. It includes continuous counts of specific interventionist behaviors from which three focal behavioral fidelity indices are computed (i.e., R:Q, %OQ, %CR).

#### ‘Gold-standard’ technical assistance

Modeled after efficacy trial procedures, TMCU interventionists assigned to this condition will attend a weekly videoconference. The purveyor (DW) will lead discussion of her review of behavioral fidelity indices and excerpts of recently conducted sessions. If interventionist drift is identified in a reviewed session, this will prompt (1) conceptual review of relevant TMCU skills, (2) purveyor demonstration, and (3) behavioral rehearsal by the interventionist.

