### Units of analysis and measures

Trial measurement includes students nested in interventionist caseloads, which in turn are nested in schools. Units of analysis exist at three levels: school, interventionist, and student. Corresponding data collection instruments are listed in Table 2.

**Table 2 Tab2:** Trial measurement instruments and processes

Unit of analysis	Instrument/process	Respondent(s)	Timing of assessment
Schools			
	Implementation leadership scale [62]	School staff members	Trial outset
	Implementation climate scale [63]	School staff members	Trial outset
	Site visit including elicitation interview with school leadership	Principal, other leaders	Trial outset
	Exit interview	Principal, other Leaders	Trial conclusion
Interventionists			
	Demography and background	Interventionists	Pre-training
	MI knowledge/attitudes test [64]	Interventionists	Pre/post-training + 6-, 12-, 18-, 24-month
	Adoption readiness scale [65]	Interventionists	Pre/post-training + 6-, 12-, 18-, 24-month
	Fidelity-rated interaction with a standardized patient [66]	Interventionists	Pre/post-training + 6-, 12-, 18-, 24-month
	Training satisfaction survey	Interventionists	Post-training
	TA satisfaction survey	Interventionists	6-, 12-, 18-, 24-month
	Interventionist time-log	Interventionists	Weekly, over 24 months
Students			
	Demography and locator data	Students	Baseline
	Normative perceptions [67, 68]	Students	Baseline
	Life goals [69]	Students	Baseline
	Global Appraisal of Independent Needs [70]	Students	Baseline, 3- and 6-month
	Marijuana Problems Scale [71]	Students	Baseline, 3- and 6-month
	Marijuana Motives Measure [72]	Students	Baseline, 3- and 6-month
	Self-efficacy to Avoid Marijuana [73]	Students	Baseline, 3- and 6-month
	Student Academic Self-Report [74]	Students	Baseline, 3- and 6-month
	Student Engagement Instrument [75]	Students	Baseline, 3- and 6-month
Investigators			
	Technical Assistance Time-Log	Purveyor	Weekly, over 24 months
	Stages of Implementation Completion Checklist [76]	Research coordinator	Continual

Trial design proposes recruitment of approximately ten schools, with 2–4 interventionists recruited per participating school to garner an intended sample of TMCU interventionists (*N* = 30) randomized to ‘gold-standard’ or ‘as-needed’ technical assistance conditions; Self-referring students (*N* = 250) will be randomized in a 2:1 ratio to receive the TMCU intervention vs. waitlist/control

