#### ‘As-needed’ technical assistance

The purveyor (DW) will initiate individual sessions by videoconference at points when the fidelity alarm bell is triggered by unacceptable drift in one or more behavioral fidelity indices (i.e., R:Q, %OQ, %CR). The alarm will be calibrated using process control benchmarking, with interventionist performances compared against index distributions of research therapists from efficacy trials. For each fidelity index, these distributions will specify an a priori lower control limit to reflect the poorest acceptable TMCU fidelity. Interventionist performances that breach such limits will trigger the alarm, prompting ‘as-needed’ remediation. Technical assistance activities will mirror those of ‘gold-standard’ sessions (i.e., conceptual review, purveyor demonstration, interventionist behavioral rehearsal).

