### Hypothesis testing and analytic approach

Hypotheses focus on comparative utility of two technical assistance methods on implementation outcomes among TMCU interventionists and intervention effectiveness among students. Hypothesized effects are that the (1) longitudinal effects of interventionists receiving ‘gold-standard’ vs. ‘as-needed’ technical assistance will not differ, with the latter method proving more cost-beneficial and cost-effective; and (2) effects of technical assistance method for intervention impact on student marijuana use frequency will not differ, with greater reduction expected of students randomly assigned to TMCU vs. waitlist/control.

Trial analyses will be governed by an investigative team member (KK), experienced as a biostatistician and methodologist in adolescent health research. Given nesting of trial data (i.e., repeated observations of students, nested in interventionist caseloads; interventionists nested in schools), multilevel models will include progressive taxonomies in model-building. Initially, an unconditional model will estimate variance of random effects, and a subsequent unconditional growth model will identify the appropriate shape of and variability in rate of change over time for hypotheses involving repeated measures. Technical assistance condition will then be included in conditional models with predictors, with relevant covariates added to determine robustness of main effects and relative goodness-of-fit for each successive model via likelihood ratio tests and deviance statistics. Power analyses (.80, *p* < .05) inform proposed recruitment of (1) 30 interventionists to detect longitudinal effects of training and technical assistance consistent with those for other lay counselors (Cohen’s *d* = 1.00); and (2) 250 students to detect small intervention effects (Cohen’s *d* = .35) relative to waitlist/control.

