#### Hypothesis 1a: comparable utility of technical assistance methods

A non-inferiority paradigm, traditionally used to show a novel treatment is not statistically different than an established one, will test study hypotheses. This paradigm will be applied to interventionists’ longitudinal implementation outcomes, principally TMCU fidelity (i.e., R:Q, %OQ, %CR) in SP interactions but also secondary outcomes of TMCU knowledge, attitudes, adoption readiness, and satisfaction. Initial effects are consistent with training intent, with analyses testing if ‘gold-standard’ and ‘as-needed’ technical assistance produce equivalent longitudinal impacts. If (as expected) the number of schools recruited is small, they will be dummy-coded and treated as fixed effects. Point-estimates and confidence intervals from the model will be included in non-inferiority tests, examining each technical assistance method for (1) pre-post change in implementation outcomes, (2) mean implementation level by TMCU interventionists over time, and (3) differential rate of change in implementation over time. As recommended [75], a ½ standard deviation (SD) difference will serve as the a priori non-inferiority margin. If the lower bound of two-sided 95% confidence interval of between-method differences exceeds this margin, a test of superiority will specify the direction and magnitude of differential impact of the technical assistance methods.

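### One arm receives assistance in a group and the other individually, but the stated models have no assistance-group level; if outcomes within a group are positively correlated, the Hypothesis 1a interval is too narrow.

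*Protocol article*

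**What the plan says.** Interventionists are randomized individually to one of two assistance methods (protocol article, Staff randomization). That section, and the closing paragraph of the Background, make gold-standard assistance a weekly group session. The ‘Gold-standard’ technical assistance section adds that "TMCU interventionists assigned to this condition will attend a weekly videoconference", with discussion led by the purveyor. In the other arm the purveyor "will initiate individual sessions by videoconference" when the fidelity alarm is triggered. The time-log section has the purveyor record individual or group assistance.

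The section Hypothesis testing and analytic approach names the data structure that the multilevel models are to respect: "repeated observations of students, nested in interventionist caseloads; interventionists nested in schools". Hypothesis 1a adds that schools become dummy-coded fixed effects if they are few. No section names the assistance group as a level, says how many gold-standard groups will run, or gives a correlation within them.

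The non-inferiority decision uses the "lower bound of two-sided 95% confidence interval of between-method differences", and "a ½ standard deviation (SD) difference will serve as the a priori non-inferiority margin".

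**The concern.** Members of a standing weekly group hear the same discussion, watch the same demonstrations and share the same group dynamics over 24 months. Their later fidelity scores may resemble one another for reasons unrelated to the individual interventionist. The as-needed arm has no such shared exposure. Where one arm is grouped and the other is not, the mean of the grouped arm can carry extra variance that a model without a group term does not see.

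School dummies do not stand in for the missing term: interventionists are randomized individually, and nothing in the article ties a group to a school.

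The direction matters. An understated standard error pulls the confidence limit inward and makes it easier to clear the margin. The error therefore favours concluding that the cheaper method is acceptable, which is the result the trial expects.

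**Working it through.** **Inputs from the protocol article.** The plan is "to garner an intended sample of TMCU interventionists (*N* = 30) randomized to ‘gold-standard’ or ‘as-needed’ technical assistance conditions". The margin is 0.5 SD and the interval is two-sided 95%, so the nominal one-sided error is 2.5%. For sample size, "Power analyses (.80, *p* < .05) inform proposed recruitment" of 30 interventionists at a Cohen's d of 1.00.

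**Assumptions.** 15 per arm (no staff allocation ratio is stated); SD 1 for the per-interventionist summary being compared; normal approximation; within-group correlation ρ from 0 to 0.10; either one gold-standard group of m = 15 or three groups of m = 5. The article gives neither ρ nor m.

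**Reproducing the plan's figure.** With independent interventionists, n per arm = 2(1.96 + 0.84)² / 1² ≈ 15.7, so 16 per arm and 32 in all. At 15 per arm the standard error is √(2/15) = 0.365 and power is Φ(1/0.365 − 1.96) = 0.78. The stated 30 is thus reproduced to within 2 without any allowance for grouping.

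**True standard error of the method difference.** The gold-standard mean has variance (1 + (m − 1)ρ)/15 and the as-needed mean 1/15, so

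true SE = √[(2 + (m − 1)ρ)/15].

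**Standard error reported without a group term.** In the gold-standard arm the model sees only the spread around the arm mean, whose expected variance is 1 − (m − 1)ρ/14. Hence

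model SE = √[(2 − (m − 1)ρ/14)/15].

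**False non-inferiority when the true difference lies exactly at the margin** = Φ(−1.96 × model SE / true SE).

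| Groups | ρ | True SE | Model SE | Ratio | False non-inferiority |
|---|---|---|---|---|---|
| any | 0 | 0.365 | 0.365 | 1.00 | 2.5% |
| three of 5 | 0.01 | 0.369 | 0.365 | 1.01 | 2.6% |
| three of 5 | 0.05 | 0.383 | 0.364 | 1.05 | 3.1% |
| three of 5 | 0.10 | 0.400 | 0.363 | 1.10 | 3.8% |
| one of 15 | 0.01 | 0.378 | 0.364 | 1.04 | 2.9% |
| one of 15 | 0.05 | 0.424 | 0.361 | 1.18 | 4.8% |
| one of 15 | 0.10 | 0.476 | 0.356 | 1.34 | 7.1% |

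Worked line, one group, ρ = 0.05: true SE = √(2.70/15) = 0.424; model SE = √(1.95/15) = 0.361; ratio 1.18; Φ(−1.96/1.18) = 4.8%.

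Using the independence value 0.365 as the reference SE instead gives a ratio of 1.16 and an error of 4.6% for that line, so the reading is the same.

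**Can a group term be estimated?** With two or more groups, yes, though on very few degrees of freedom. With one group, no: group and method coincide, and the data cannot separate them.

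**The case against.** A reader might infer that the interval *is* too narrow. The documents do not support that: it needs a positive within-group correlation, and none is given. At zero the effect disappears, and with several small groups it is modest. The larger figures require all gold-standard interventionists to sit in one group for two years, which the article does not say.

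A reader might also infer that a group random effect cures the problem, or that the verdict should have to survive a fixed widening of 1.18. Neither follows. With one group the term cannot be identified, and 1.18 belongs to one assumed correlation and one assumed group size.

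The amount of sharing is also open to argument. Remediation is tied to drift in an interventionist's own reviewed session, the as-needed activities are meant to match the gold-standard ones, one purveyor oversees both arms, and fidelity is scored by blinded raters from individual standardized-patient encounters. The pre- and post-training assessments precede randomization to assistance, so group correlation can arise only at follow-up. The calculation above compares single means, whereas Hypothesis 1a names pre-post change, mean level and rate of change; the relevant correlation is that of each summary. These points stand as limits on size.

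Finally, a condensed article may leave model detail to an analysis plan that is not shown. That carries less weight here, because the nesting is stated explicitly as the reason for the models and this level is absent from it.

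**Conclusion.** The point holds in conditional form. The design is partially nested, and the stated models omit the level at which gold-standard assistance is delivered. If outcomes within a gold-standard group are positively correlated, the Hypothesis 1a interval is too narrow and false non-inferiority exceeds 2.5%: about 3.1% to 3.8% with three groups of five and about 4.8% to 7.1% with one group of 15, for correlations of 0.05 to 0.10. The correlation, the number of groups and the 15 per arm are all assumptions, so these are illustrative ranges and not estimates for this trial. What can be said firmly is the direction of the error and that the stated model would not detect it.

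**What to change.** In the technical assistance sections, state how many gold-standard groups will run, and record each interventionist's group membership.

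- **Two or more groups:** under Hypothesis 1a, fit a group random effect in the gold-standard arm only, with as-needed interventionists as singletons, and use small-sample degrees of freedom.
- **One group:** say under Hypothesis 1a that the group's effect cannot be separated from the method and that the non-inferiority conclusion is conditional on that group. Report a sensitivity analysis with the standard error inflated over a range of assumed correlations, for example 0.01 to 0.10, and show whether the conclusion changes. Do not make the verdict depend on a single fixed factor.

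The cost is one variable and a few sentences. The downside is a wider, less favourable interval, and with only two or three groups an imprecise group variance.
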